**Fig. 1 Fig1:**
[figure not shown]
Trial design

One hundred women will be randomised to either receive the intervention immediately, or after the 3-month follow-up period. People will be eligible for inclusion in the trial if they are female, aged 50 years and over, employees of The University of Sydney or Sydney Local Health District in Australia. Potential participants will be excluded if they have limited English language skills, or have a medical condition that precludes participation in regular physical activity, or are already sufficiently active in accordance with the Australian Physical Activity guidelines [8]. Potential participants will be provided with a participant information statement outlining the study procedures. All participants will sign a consent form before participating in the study.

Participant recruitment will be through advertising using the workplace channels at the university and health service. This will be via university newsletters and websites, the health service intranet, posters and email invitations sent to managers of university and hospital departments for distribution to their employees. No workplace incentives will be offered for participation in this study. People who wish to participate in the research project will be screened for eligibility either over the telephone or via email.

Participants will be enrolled into the study after they have completed the initial screening, provided informed written consent to participate in the project, and have completed all baseline questionnaires and measurements of physical activity.

Baseline questionnaires will be sent to participants via an online survey link (*REDCap*) or by post, as preferred by the participant. Baseline physical activity will be measured with an *Actigraph* accelerometer. A research team member who is blind to study group allocation will download the accelerometer data. Each participant will receive a study enrolment number upon completing the baseline questionnaire generated by the *REDCap* database and this will be recorded on all study documents.

Following completion of the baseline measures, participants will be randomly allocated to:
participation in one information session plus follow-up support immediately (intervention group) orparticipation in one information session plus follow-up support after the 3-month follow-up period (control group)

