A variable block randomisation schedule will be prepared from a computer-generated list of random numbers by a researcher not involved in recruitment. The randomisation schedule will incorporate stratification for recruitment site (University campus, Sydney Local Health District) or pairs. Where there are two participants who are known to each other or if they are from the same workplace department as revealed by the initial contact, they will be randomised to the same group to reduce cross-contamination of the results. The randomisation schedule will be embedded in a secure online database (*REDCap*) to achieve allocation concealment.

The intervention group will attend a one-hour information session that will provide: 1) information about the importance of physical activity for maximising physical and mental health and preventing disability; 2) group discussion in overcoming the barriers to physical activity; 3) information and handbook of resources about existing opportunities for women over 50 years to participate in; 4) video case-study interviews of four female staff members aged over 50, and one female staff member aged over 80 who have overcome barriers to increase their physical activity; 5) tools to enhance physical activity participation (e.g. physical activity recording charts, guidance on goal setting), 6) the use of a pedometer or internet-connected activity tracker (*Fitbit*) for the duration of the study, to provide motivation and feedback to increase activity levels if desired, and 7) a free trial class at the university sports facility. An online discussion group will be set up for participants who wish to remain in contact, and a fortnightly email from the research team will be sent to provide information, motivation and support. The information session and follow-up email support will emphasise strategies to overcome barriers to participation. These will include incorporating physical activity into daily life through active transport, incidental physical activity and benefits to health and habit formation of even small increases in physical activity. The information session materials and sample physical activity recording charts will also be made freely available to participants.

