Participants randomised to the control group will be allocated to a waiting list and will receive access to the intervention after the 3-month follow-up period.

The primary outcome will be the proportion of people achieving an average of at least 10,000 daily steps, measured objectively with a matchbox-sized waist-worn accelerometer (*Actigraph GT3X+*) at 3-months. *ActiGraph GT3X+* is able to accurately estimate how physically active a person is throughout the day by measuring 3D body accelerations and is a valid instrument that has been extensively researched in the physical activity and public health field [27]. Participants will be instructed to wear the accelerometer on the right hip, attached via an adjustable elastic belt, for seven consecutive days during waking hours (except during water-based activities or bathing), and to complete an activity log. Activity counts per second will be collected at a sampling frequency of 30 Hz and reintegrated to 60s epochs for data analysis.

The primary outcome will be quantified as the average step counts per day. This outcome will detect any increase in incidental physical activity (i.e. less time spent sitting) as well as adoption of more formal exercise regimens. These data will be collected over a 7-day period to account for day-to-day variation in physical activity levels. The accelerometers will be posted to participants with clear instructions for use and email or telephone support will be available. Participants will be provided with pre-paid envelopes to return the devices to the research centre. Accelerometer data will be manually checked against participant activity logs to verify wear time, and erroneous data will be excluded prior to analysis. Physical activity participation will be assessed at baseline and 3 months after participant randomisation, and *ActiGraph* data will be extracted by a research assistant who is unaware of group assignment (i.e. blinded outcome assessment).

Accelerometer data will be analysed using *ActiLife 6* software. Acceptable wear time will be defined as 4 days or more of 10 h or more per day. Periods of 90 min or more of consecutive zeros (indicating non-use) will be considered as non-wear time.

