The secondary outcomes will be assessed at baseline and at 3 months post-randomisation via a self-report questionnaire that will take approximately 30 min to complete. The secondary outcomes will include: 1) the proportion of people achieving adequate physical activity levels as recommended by national physical activity guidelines: 150 to 300 min of moderate intensity physical activity or 75 to 150 min of vigorous intensity physical activity, or an equivalent combination of both moderate and vigorous activities, each week, and to do muscle strengthening activities on at least 2 days each week [7], measured using an *Actigraph* accelerometer; 2) the average total number of hours of physical activity per week, self-reported with the International *Physical Activity Questionnaire* (IPAQ) [32]; 3) change in perceived benefits of and barriers to exercise participation, as measured by the *Exercise Benefits and Barriers Scale* [33]; 4) physical functioning as measured by the function component of the *Late Life Function and Disability Instrument* (LLFDI) [34]; 5) mood as measured with the *Positive and Negative Affect Schedule* (PANAS) [35]. Participants in the intervention group will also complete a follow-up questionnaire evaluating whether the suggested or other resources were investigated or participated in, whether goals were set, and participants’ perceived barriers and plans following the workshop.

Odds ratios will be calculated to assess the effect of group allocation on the dichotomously-scored primary outcome (proportion of people achieving 10,000 steps/ day) and secondary outcome (proportion of people achieving physical activity in accordance with national guidelines). General linear models will assess the effect of group allocation on the continuously-scored secondary outcomes (self-reported physical activity, perceived exercise benefits and barriers, physical functioning and mood), adjusting for baseline scores.

A *p*-value of < 0.05 will be considered statistically significant. A full statistical analysis plan will be devised by the lead investigator prior to commencement of data analysis. Analyses will be pre-planned, conducted while masked to group allocation and will use an intention-to-treat approach. Analyses will be conducted using the *Stata 14* software package.

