## Discussion

The evidence for the physical and mental benefits of physical activity, even in small amounts [9, 37, 28] in delaying the development of disability and chronic disease is compelling, yet the problem of physical activity participation remains a significant global public health dilemma.

This study targets women over the age of 50, a group that is at greatest risk of developing disability in older age, who are insufficiently active according to the national physical activity guidelines [8]. The trial will provide evidence on the impact of a brief, low-dose, low-cost intervention to address the problem of physical inactivity in the workplace setting, an ideal setting due to the amount of time spent at work, the potential risk that work may contribute to inactivity, and possible benefits that the intervention may have on employee wellbeing [17].

The intervention will provide support for behaviour change through the BCW framework. Behavioural change and adherence to the program will be facilitated, enabled and supported by providing the group information session face-to-face or online, opportunities for discussion, inspiration through video case studies, post-workshop support with the provision of a resource handbook, use of an activity tracker (*Fitbit*) and workshop materials, receiving fortnightly email messages, joining an online discussion group, and a free trial class at the university sports facility.

A limitation of this trial is that participants will be recruited based on self-rated physical activity prior to objective physical activity baseline measures. Other limitations are that only land-based physical activities will be measured by the accelerometer, a lack of individual tailoring of the intervention, and limited generalisability of this sample to other workplace settings and to men.

However, if found effective, this low-cost program with supported follow-up, could be scalable, directly implemented into the workplace setting and directly address the problem of physical inactivity. There would also be scope for this intervention to be translated to the broader community by exploring other settings and resource delivery.

An effective and scalable preventive health strategy is needed to ease the burden on health systems already at capacity, and burden on individuals’ lives. This simple intervention has the potential to address the problem of physical inactivity to delay the onset of disability in older age.

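### Baseline adjustment is specified for the continuous secondary outcomes but not for the primary odds ratio, although baseline steps are measured on every woman before randomisation

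*Protocol article*

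**What the plan says.** All places are in the protocol article.

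- **Primary outcome (Methods).** "The primary outcome will be the proportion of people achieving an average of at least 10,000 daily steps", measured by hip-worn accelerometer at 3 months. It is status at follow-up, not change from baseline.
- **Primary analysis (Methods, statistical analysis).** "Odds ratios will be calculated to assess the effect of group allocation on the dichotomously-scored primary outcome". The same sentence covers the dichotomous secondary outcome. No model or covariate is named.
- **Continuous secondary outcomes (the next sentence).** General linear models are planned for these ("self-reported physical activity, perceived exercise benefits and barriers, physical functioning and mood), adjusting for baseline scores").
- **Baseline steps (Methods, enrolment).** "Baseline physical activity will be measured with an *Actigraph* accelerometer". Women are enrolled only once they "have completed all baseline questionnaires and measurements of physical activity", and randomisation follows.
- **Entry screen (Methods and Discussion).** Women who already meet the national activity guideline are excluded. The Discussion lists as a limitation that "participants will be recruited based on self-rated physical activity prior to objective physical activity baseline measures". No criterion refers to steps.
- **Randomisation (Methods).** "The randomisation schedule will incorporate stratification for recruitment site (University campus, Sydney Local Health District) or pairs".
- **Sample size (Methods).** 50 per group for 80% power to detect 30 percentage points above a 27% control rate, with 5% alpha and 15% dropout.
- **Deferral.** A full statistical analysis plan is to be written before data analysis begins. It is not shown.

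**The concern.** Two consecutive sentences treat baseline differently. The authors went into enough detail to name baseline adjustment, and attached it only to the continuous secondary outcomes. The natural reading is that the primary odds ratio is unadjusted, and the sample size, which is an unadjusted two-proportion calculation, fits that reading.

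This matters because of how women enter the trial. The screen asks about guideline activity, by self-report, and the outcome is a step count. A woman who walks a great deal may still consider herself insufficiently active, enter at or above 10,000 steps, and be likely to remain there at 3 months. A chance excess of such women in one arm would shift the primary result. The measurement needed to allow for this is taken with the same device, on everyone, before allocation. At stake are the precision of the primary comparison and its protection against chance imbalance.

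**Working it through.** **1. The plan's own sample size.** Inputs (Methods, sample size): p0 = 0.27, p1 = 0.27 + 0.30 = 0.57, alpha 5% (taken as two-sided), power 80%, dropout 15%. With mean proportion 0.42:

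n = [1.960 × √(2 × 0.42 × 0.58) + 0.842 × √(0.27 × 0.73 + 0.57 × 0.43)]² / 0.30²

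= [1.960 × 0.698 + 0.842 × 0.665]² / 0.09 = 1.928² / 0.09 ≈ 41.3, so 42 per group.

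Dropout: 42 / 0.85 = 49.4, so 50 per group. The stated figure reproduces. Power of this test with 42 per group is 80.7%. An unadjusted comparison therefore meets the plan's target on its own inputs.

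**2. Scale of chance imbalance.** The documents do not say how many entrants already reach 10,000 steps. As an illustration, assume the 27% control rate, which itself comes from baseline data on university staff, also holds at entry. The between-arm difference in that proportion then has standard deviation

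- 50 per arm: √(2 × 0.27 × 0.73 / 50) = 0.089, or 8.9 points;
- 42 per arm: √(2 × 0.27 × 0.73 / 42) = 0.097, or 9.7 points.

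One standard deviation is about 0.3 of the 30-point design effect (8.9 / 30 = 0.30; 9.7 / 30 = 0.32). It does not carry through to the outcome one for one, because a woman above the threshold at entry can be below it at 3 months.

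**3. What adjustment would gain.** The documents give no correlation r between baseline and 3-month steps, so a range was assumed. The set-up was 2,000 simulated trials per setting, 42 completers per arm, normally distributed latent steps, 27% against 57% at the threshold, and a likelihood-ratio test of group in logistic regression with and without continuous baseline steps.

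| Assumed r | Power, unadjusted | Power, adjusted | Type I error, unadjusted | Type I error, adjusted |
|---|---|---|---|---|
| 0.3 | 84.1% | 83.5% | 4.8% | 5.0% |
| 0.5 | 83.3% | 87.8% | 4.7% | 5.1% |
| 0.7 | 83.3% | 93.6% | 5.6% | 6.2% |

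A separate run of the same design gave 84% against 84%, 83% against 88% and 83% against 93%, with adjusted type I error of 5.5–5.8%. The Monte Carlo standard error of a power near 83% is √(0.83 × 0.17 / 2000) = 0.8 points, so the r = 0.3 row shows no gain. These figures come from a different test from the formula in step 1, so the fair comparison is within each row. Recruitment site was not part of the simulation.

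**4. Scale of the effect measure.** At the design values the odds ratio is (0.57 / 0.43) / (0.27 / 0.73) = 3.58, the risk ratio is 0.57 / 0.27 = 2.11, and the difference is 30 points. The trial is sized on the last of these.

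**The case against.** The strongest reply is that the article never calls the odds ratio unadjusted. An adjusted logistic model also yields an odds ratio, and covariates are commonly left to the analysis plan, which is promised and not shown. That stands as far as certainty goes: the unadjusted reading is an inference. What it does not remove is the published contrast. Once baseline adjustment is written down for some outcomes and not for the primary one, adding it later without an explicit statement would look like a departure from the protocol.

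Second, nothing fails by the plan's own figures. This also stands. A reader might infer that the primary analysis is biased or underpowered. Randomisation makes the unadjusted comparison unbiased, its standard error already allows for chance imbalance, and step 1 shows that it reaches the stated 80%. What is lost is a possible gain above that level.

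Third, the gain depends on an undocumented correlation and vanishes at r = 0.3. That is correct and limits the claim.

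Three other tempting readings go too far:

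- **That the plan leaves the stratification factor out of its analyses.** No analysis in the article mentions site or pairs at all, so this rests on silence alone.
- **That a woman above 10,000 steps at entry is a success in either arm.** The outcome is measured at 3 months, so she must still average 10,000 then. She is likely to, not certain to.
- **That naming an odds ratio is an error because the trial is sized on a difference.** The article does not say that only an odds ratio will be reported, and the proportions by arm would give the difference. This is a reporting preference.

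**Conclusion.** The point holds as an improvement available at almost no cost, not as an error that invalidates the trial. The article names baseline adjustment for the continuous secondary outcomes and no covariate for the primary odds ratio, while baseline steps are in hand for every woman before allocation and the entry screen does not exclude those already at the threshold. An unadjusted analysis is valid and adequately powered on the plan's inputs, but less precise than it could be.

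The gain in power is about 0 points at r = 0.3, 4 to 5 points at r = 0.5 and 10 points at r = 0.7, with adjusted type I error of about 5–6%. These figures assume latent-normal steps, 42 completers per arm, the design rates of 27% and 57%, and correlations that the documents do not supply. The imbalance figures in step 2 further assume that 27% of entrants are already at the threshold.

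**What to change.** State the primary analysis, in the statistical analysis plan and before data analysis begins, as logistic regression of reaching 10,000 steps/day at 3 months on group and baseline mean daily steps (continuous). Add recruitment site because randomisation stratifies on it.

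The adjusted odds ratio is conditional on the covariates and will differ from the unadjusted one even when the arms are perfectly balanced. Report beside it the marginal (standardised) risk difference with its 95% CI, which is on the scale of the 30-point design effect. A table of women at or above 10,000 steps at baseline, by arm, would help readers judge the result.

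The cost is wording only. No new data are needed, and the sample size can stay at 50 per group.

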## Discussion

The evidence for the physical and mental benefits of physical activity, even in small amounts [9, 37, 28] in delaying the development of disability and chronic disease is compelling, yet the problem of physical activity participation remains a significant global public health dilemma.

This study targets women over the age of 50, a group that is at greatest risk of developing disability in older age, who are insufficiently active according to the national physical activity guidelines [8]. The trial will provide evidence on the impact of a brief, low-dose, low-cost intervention to address the problem of physical inactivity in the workplace setting, an ideal setting due to the amount of time spent at work, the potential risk that work may contribute to inactivity, and possible benefits that the intervention may have on employee wellbeing [17].

The intervention will provide support for behaviour change through the BCW framework. Behavioural change and adherence to the program will be facilitated, enabled and supported by providing the group information session face-to-face or online, opportunities for discussion, inspiration through video case studies, post-workshop support with the provision of a resource handbook, use of an activity tracker (*Fitbit*) and workshop materials, receiving fortnightly email messages, joining an online discussion group, and a free trial class at the university sports facility.

A limitation of this trial is that participants will be recruited based on self-rated physical activity prior to objective physical activity baseline measures. Other limitations are that only land-based physical activities will be measured by the accelerometer, a lack of individual tailoring of the intervention, and limited generalisability of this sample to other workplace settings and to men.

However, if found effective, this low-cost program with supported follow-up, could be scalable, directly implemented into the workplace setting and directly address the problem of physical inactivity. There would also be scope for this intervention to be translated to the broader community by exploring other settings and resource delivery.

An effective and scalable preventive health strategy is needed to ease the burden on health systems already at capacity, and burden on individuals’ lives. This simple intervention has the potential to address the problem of physical inactivity to delay the onset of disability in older age.

## Data Availability

Not applicable.

## Abbreviations

BCW: Behaviour Change Wheel
CONSORT: Consolidated Standards Of Reporting Trials statement
SPIRIT: Standard Protocol Items: Recommendations for Interventional Trials statement
TIDieR: Template for Intervention Description and Replication checklist
